## Abstract

**Background:**

Early-onset hip osteoarthritis is commonly seen in people undergoing hip arthroscopy and is associated with increased pain, reduced ability to participate in physical activity, reduced quality of life and reduced range of motion and muscle strength. Despite this, the efficacy of non-surgical interventions such as exercise therapies remains unknown. The primary aim is to establish the feasibility of a phase III randomised controlled trial investigating a targeted physiotherapy intervention for people with early-onset hip osteoarthritis. The secondary aims are to determine the size of treatment effects of a physiotherapy intervention, targeted to improve hip joint range and hip-related symptoms in early-onset hip osteoarthritis following hip arthroscopy, compared to a health-education control.

**Methods:**

This protocol describes a randomised, assessor- and participant-blind, controlled clinical trial. We will include 20 participants who are (i) aged between 18 and 50 years; (ii) have undergone hip arthroscopy during the past six to 12 months; (iii) have early-onset hip osteoarthritis (defined as chondrolabral pathology) at the time of hip arthroscopy; and (iv) experience hip-related pain during activities. Primary outcome will be the feasibility of a phase III clinical trial. Secondary outcomes will be (i) perceived global change score; (ii) hip-related symptoms (measured using the Hip disability and Osteoarthritis Outcome Score (HOOS) pain subscale, activity subscale, and sport and recreation subscale); (iii) hip quality of life (measured using the HOOS quality of life subscale and International Hip Outcome tool; (iv) hip muscle strength and (v) hip range of motion. The physiotherapy intervention is semi-standardised, including joint and soft tissue mobilisation and stretching, hip and trunk muscle retraining and functional and activity-specific retraining and education. The control intervention encompasses individualised health education, with the same frequency and duration as the intervention. The trial primary end-point is the conclusion of the 12-week intervention, and follow-up measures will be collected at the 12-week post-baseline assessment.

**Discussion:**

The findings of this study will provide guidance regarding the feasibility of a full-scale phase III randomised controlled trial, prior to its undertaking.

**Trial registration:**

The trial protocol was registered with the Australian Clinical Trials Registry (number: 12614000426684) on 17 April 2014.

**Electronic supplementary material:**

The online version of this article (doi:10.1186/s13063-014-0543-7) contains supplementary material, which is available to authorized users.

## Background

Hip pathology is a common cause of hip pain [1,2], and is associated with considerable morbidity in people aged between 18 and 50 years [3,4]. In recent years, arthroscopic surgery has contributed to advancements in assessment and management of hip pain [5]. Recently, the number of hip arthroscopic procedures performed in the United States [6-8], United Kingdom, Australia [9] and Asia [10] has increased dramatically. In Australia, Medicare data indicate that between 2010 and 2013 the number of people undergoing hip arthroscopy increased by over 50% [9], while in the United States the rate of hip arthroscopic surgery increased six-fold between 2006 and 2010 [7]. Despite good results at between five and 10 years post-arthroscopy years, those with osteoarthritis (OA) at arthroscopy consistently report less favourable outcomes when compared to those without OA [11]. In addition, we recently observed that early-onset hip OA is associated with worse outcomes in people who have undergone hip arthroscopy [12].

Musculoskeletal conditions are second only to mental and behavioural disorders, as global contributors to years lived with disability [13]. Due to its negative impact on individual functioning and health service expenditure, OA has been designated a National Health priority area [14]. The hip joint is a common site for OA [15], affecting approximately 12% of adults in the United Kingdom [16] and the United States of America [17]. As there is no cure for hip OA, the identification of non-surgical interventions that can reduce the progression of hip-related symptoms is important, as this will reduce disease burden [18].

We recently reported that chondrolabral pathology, a marker of early-onset hip OA, is common in people who undergo hip arthroscopy for hip pain, and is associated with worse pain, difficulty participating in physical activity and reduced quality-of-life compared to healthy controls [19]. Moreover, it appears that early onset hip OA has a significant impact on young and middle-aged people being able to participate in physical activities without difficulty, which could ultimately lead to physical inactivity. Inactivity is associated with adverse health outcomes, which include type two diabetes, ischaemic heat disease, stroke, depression and certain cancers [20]. If the progression of hip OA symptoms can be slowed in its early stages, people with hip OA may participate in greater levels of physical activity, limiting the public health burden of this disease [21,22].

A full-scale phase III randomised controlled trial (RCT) is costly, and before undertaking such a study it is important to establish its feasibility [23,24]. In Australia, hip arthroscopy is mostly conducted in the private sector and such patients may be unwilling to participate in an RCT. In addition, no RCT examining the effects of a physiotherapy intervention has been undertaken in this population, and adherence with the intervention is unknown. The treatment algorithm has not been tested within the constraints of a clinical trial and the adverse events are not known. Therefore, before committing to a full-scale RCT, the feasibility of such a study should be established by undertaking a phase II RCT [24].

The primary aim of this study is to establish the feasibility of a phase III RCT investigating a targeted physiotherapy intervention for people with early-onset hip OA. The secondary aims are to determine the size of treatment effects of a physiotherapy intervention, targeted to improve hip joint range and hip-related symptoms in early-onset hip OA following hip arthroscopy, compared to a health-education control.

## Methods/Design

### Experimental design

This protocol describes a randomised, assessor- and participant--blind, controlled clinical trial conforming to Standard Protocol Items: Recommendations for Interventional Trials (SPIRIT) [25] guidelines. The trial protocol was registered with the Australian Clinical Trials Registry (ACTR number: 12614000426684) on 17 April 2014. Ethics approval was obtained through the University of Queensland Medical Research Ethics Committee (number: 2013001553).

### Participants

A total of 20 participants will be recruited through a single orthopedic surgeon ([name]) in Hobart, Australia, with extensive expertise in hip arthroscopy. This number of participants was chosen in order to determine the feasibility of recruitment into a larger scale phase III trial, as we estimate that 20 participants represents 30% of eligible patients from a single surgeon. In addition, 20 participants will allow for observation of sample variability and any possible adverse responses to the intervention. A project investigator (KM) will screen for eligibility based on history and examination.

#### Inclusion criteria

The inclusion criteria are as follows: (i) aged between 18 and 50 years; (ii) arthroscopy for intra-articular hip pathology during the past six to 12 months; (iii) evidence of early-onset hip OA (defined as chondrolabral pathology) at time of hip arthroscopy; (iv) hip-related pain during activities such as sitting, squatting, stair ambulation or twisting on the leg and (v) hip-related pain score of over 30 on a 100 mm visual analogue scale (VAS).

#### Exclusion criteria

The exclusion criteria are as follows: (i) pain that is not confirmed by physical examination of the hip [26,27]; (ii) concurrent symptoms of hip bursitis or tendinitis; (iii) surgical complications, including infection; (iv) planned lower limb surgery in the following 12 months (such as an arthroplasty); (v) physical inability to weight-bear fully or undertake testing procedures and (vi) inability to understand written and spoken English.

### Procedure

Potential participants will be identified by the surgeon and invited to contact the project coordinator (JK). (Figure 1) The project coordinator will contact potential participants by phone if they do not respond to the initial invitation. Volunteers will be screened via telephone interview, followed by a clinical examination to confirm eligibility (KM). The randomisation schedule will be generated and maintained centrally by the University of Queensland, School of Health and Rehabilitation Sciences, and will be revealed to the project coordinator (JK) via telephone following the baseline assessment. The blinded researcher (KM) will obtain informed consent (Additional file 1) and will perform outcome assessments at baseline and three months. Participants will be instructed not to divulge their group allocation to the assessor. While physiotherapists cannot be blinded to group allocation, participants will be informed that they can receive one of two possible interventions. Thus, participants will remain blinded to treatment allocation. Participants will be asked to refrain from other treatments, but stable drug doses will be permitted. Physiotherapists will record per protocol treatment. Participants will record adherence with home exercises, adverse events and any co-interventions in a log book.

**Figure 1 Fig1:**
[figure not shown]
**Flowchart of trial.**

### Outcome assessment

Outcomes will be assessed at baseline and at the trial primary end-point, which is at the conclusion of the 12-week intervention.

### Primary outcome measure: feasibility of a full-scale randomized controlled trial

Feasibility will be assessed by evaluating the willingness of participants to enrol; the number of eligible participants; the recruitment rate; adherence to the intervention, home exercises and log-book completion and the drop-out rate. Adverse events will be recorded.

### Secondary outcome measures: perceived global change score

Participants will rate their perceived change following treatment on a six-point ordinal scale (completely recovered, much improved, improved, no change, worse and much worse) [28]. Measuring patient-perceived change using such scales has been shown to be clinically relevant and a stable concept for interpreting meaningful improvements from an individual perspective [29].

### Secondary outcome measure: hip-related symptoms

The Hip disability and Osteoarthritis Outcome Score HOOS-pain [30] will measure hip-related symptoms. The HOOS was evaluated in younger adults with OA [30], and incorporates the Western Ontario MacMaster Universities Osteoarthritis Index (WOMAC) 3.0LK [31]. The HOOS-pain subscale is equivalent to the WOMAC pain subscale. We have determined that the HOOS-pain subscale is reliable (intraclass correlation coefficient (ICC) = 0.96; 95% confidence interval (CI): 0.93 to 0.98), with a low standard error of measurement (SEM) of four points out of 100, and is valid and responsive, with a minimal clinically important change (MCIC) of nine points [32].

### Secondary outcome measures: hip-related quality of life

The International Hip Outcome tool (iHOT-33) and HOOS quality of life subscale (HOOS-Q) will measure hip-related quality of life. The iHOT-33 is a composite score that was developed for specific use in the hip arthroscopy population [33]. We determined that it is reliable (ICC = 0.93; 95% CI: 0.87 to 0.96), with a low SEM of six points out of 100, and is valid and responsive, with an MCIC of 10 points [32]. The HOOS-Q [30] is reliable (ICC = 0.95; 95% CI: 0.84 to 0.97), with a low SEM of five points out of 100, and is valid and responsive, with an MCIC of 11 points [32].

### Secondary outcome measures: other hip-related symptoms

Other hip-related symptoms will include the HOOS activity of daily living subscale (HOOS-A), the HOOS sport and recreation subscale (HOOS-Sp) and HOOS symptoms and stiffness subscale (HOOS-S). We determined these subscales were reliable (ICC: 0.93 to 0.96), with low SEMs of three to six points, and have MCICs ranging from six to 10 points [34].

### Secondary outcome measures: hip muscle strength and hip joint range

Hip abduction, extension and external rotation strength and hip flexion range will be measured using our previously published methods [35,36], with high reliability (ICC: 0.87 to 0.95). Briefly, all strength tests will be performed with a Commander Power track II (J-Tech medical, Salt Lake City, Utah, USA) hand-held dynamometer. The tester will match the force generated by the participant performing an isometric muscle contraction (the ‘make’ test) [37] and the best of three tests will be recorded. Strength will be recorded as a torque measure, calculated by multiplying the force (measured in Newtons (N)) by the length of the moment arm (measured in metres (m)), and then data will be normalized for body weight (measured in kilograms ((kg) Nm/kg). Specifically, abductor strength will be measured in the supine position, with stabilisation of the contra-lateral thigh, and external rotation strength will be measured in the prone position, with stabilisation of the contra-lateral thigh [35]. Hip flexion range will be measured in the supine position as an active range of motion measure, with stabilisation of the contra-lateral thigh. It will be measured using a Plurimeter inclinometer ([name], La Conversion, Switzerland) as the mean of three measures [36].

### Other measures

#### Potential covariates for statistical analyses

The potential covariates for statistical analyses are body anthropometry: weight, height, body mass index and waist girth.

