##### Data management, monitoring and statistical analyses

Treatment efficacy will be evaluated by comparing change on primary outcome measures between groups. Baseline characteristics of participating patients of the two groups will be evaluated for their influence on outcomes and included as covariates in statistical analyses if required. Outcomes of interest will be analysed on an intention-to-treat basis for all participants. SPSS software (Version 21, SPSS Inc, Chicago, IL, USA) will be used for all analyses, and significance will be set at *P* <0.05. Data monitoring will be conducted by an independent investigator (KC), and data will be stored in a locked cabinet and password-secured server. Adverse events will be recorded by the treating physiotherapists who will inform the project coordinator (JK). Trial results will be made available to participants and will be published in a peer-reviewed journal.

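### Efficacy is judged on between-group change, and the baseline score of each outcome is collected but not pre-specified as a covariate

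*Protocol article*

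**What the plan says.** Four statements in the protocol article bear on this.

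- **Contrast** (Data management, monitoring and statistical analyses): "Treatment efficacy will be evaluated by comparing change on primary outcome measures between groups". The primary outcomes are feasibility measures, which have no change from baseline, so the sentence can only work for the secondary clinical outcomes.
- **Named covariates** (Potential covariates for statistical analyses): "The potential covariates for statistical analyses are body anthropometry: weight, height, body mass index and waist girth".
- **Optional covariates** (same section as the contrast): baseline characteristics of the two groups will be examined for their influence on outcomes and adjusted for where that is judged necessary. No list and no decision rule is attached.
- **Timing of measurement** (Outcome assessment): "Outcomes will be assessed at baseline and at the trial primary end-point". Under Procedure, the allocation is disclosed to the coordinator only after the baseline assessment.

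The secondary aims include determining the size of treatment effects, and the Discussion says these will help with power calculations for later trials.

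**The concern.** For an outcome measured at both visits, its own baseline score is normally the natural covariate for the follow-up score. Here it is collected before allocation is disclosed, at no extra cost. The article instead names four body-size measures. BMI is computed from two of the others, and the strength outcomes are already normalised for body weight.

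Comparing change without further adjustment sets the slope of follow-up on baseline to 1. If the true slope is below 1, the group that happens to start higher looks as if it gained less. With about 10 participants per arm, such imbalances are often large.

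The optional clause does not settle the matter. It makes adjustment depend on what the data show, in a sample of 20. At stake is the effect-size estimate, which is meant to inform the sizing of a phase III trial.

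**Working it through.** **No figure of the plan to reproduce.** The article has no power or precision calculation. Its only sample-size reasoning is that "we estimate that 20 participants represents 30% of eligible patients from a single surgeon", which implies about 20/0.30 = 67 eligible patients.

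**Inputs**
- N = 20 (Participants). Allocation ratio not stated; **assumed** 1:1, so n = 10 per arm.
- Alpha: "significance will be set at *P* <0.05"; **assumed** two-sided.
- HOOS-pain SEM 4, ICC 0.96, MCIC 9 (section on hip-related symptoms). Implied SD = 4/√(1 − 0.96) = 20.
- rho, the baseline to week-12 correlation, is not given; **assumed** over 0.3 to 0.9. The ICC of 0.96 is a reliability coefficient, not a 12-week correlation under treatment.
- Equal SD at both visits, **assumed**; the slope of follow-up on baseline then equals rho.

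**Formulas**
- Change: Var = 2(1 − rho) × SD² × 2/n, on 18 df.
- ANCOVA: Var = (1 − rho²) × SD² × (2/n) × (1 + 1/(N − 4)), on 17 df. The last factor, 1 + 1/16 = 1.0625, is the expected cost of estimating the slope.
- Variance ratio, ANCOVA/change: (1 + rho)/2 in large samples; times 1.0625 at N = 20.
- Given a baseline difference d, the change estimate is off by −(1 − rho) × d.
- SE of the baseline difference: 20 × √(2/10) = 8.94 points, about one MCIC.

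**Example at rho = 0.5**
- Change SE = √(2 × 0.5 × 400 × 0.2) = 8.94.
- ANCOVA SE = √(0.75 × 400 × 0.2 × 1.0625) = 7.98.
- Shift from a one-SE imbalance = 0.5 × 8.94 = 4.5 points.

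| rho | SE change | SE ANCOVA | Variance ratio, large sample | Variance ratio, N = 20 | 95% CI half-width, change vs ANCOVA | Shift in change estimate, one-SE imbalance |
|---|---|---|---|---|---|---|
| 0.3 | 10.58 | 8.79 | 0.65 | 0.69 | 22.2 vs 18.6 | 6.3 |
| 0.5 | 8.94 | 7.98 | 0.75 | 0.80 | 18.8 vs 16.8 | 4.5 |
| 0.7 | 6.93 | 6.58 | 0.85 | 0.90 | 14.6 vs 13.9 | 2.7 |
| 0.9 | 4.00 | 4.02 | 0.95 | 1.01 | 8.4 vs 8.5 | 0.9 |

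At N = 20 the ratio reaches 1 when 1.0625 × (1 + rho)/2 = 1, that is at rho = 0.88. At rho 0.96 it is 1.04.

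**Simulation check** (40,000 trials at each of rho 0.5, 0.7 and 0.9)
- SD of the estimate, change vs ANCOVA: 8.93 vs 7.95, 6.92 vs 6.59, 3.99 vs 4.00.
- Among trials with a baseline difference within 1 point of 9, mean error of the change estimate: −4.7, −2.7 and −0.9. For ANCOVA: −0.3, −0.1 and 0.0.

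**Sensitivity to the SD.** The variance ratios do not depend on the SD, and the shifts are proportional to it. For iHOT-33 the implied SD is 6/√0.07 = 22.7, so a one-SE imbalance is 10.1 and the shift at rho 0.5 is 5.1. For HOOS-Q, 5/√0.05 = 22.4 gives 10.0 and 5.0. If the pain threshold for entry narrowed the HOOS-pain SD to 15 (assumed), the figures would be 6.7 and 3.4.

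**The case against.** A reader might infer that the plan admits only body-size covariates and will not use the baseline score. The article does not support that. The body-size list is one of potential covariates placed among additional measures, and it does not claim to be complete. The optional clause is broader, and a baseline HOOS or strength score can be read as a baseline characteristic. A regression of change on group and baseline score also gives the same treatment estimate and standard error as a regression of the week-12 score on the same terms. The stated contrast is therefore compatible with a proper ANCOVA. What stands against the plan is narrower: the adjustment is not committed to in advance.

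A second objection is that a condensed article may leave model terms to the analysis plan. That would answer a complaint about silence. Here the article does state a contrast, a covariate list and a way of choosing covariates, and these can be judged as stated.

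A third objection concerns size, and much of it stands.
- Over randomisation as a whole the change contrast is unbiased; the shifts above are conditional on an imbalance that has occurred.
- The large-sample ratios of 0.65, 0.75 and 0.85 overstate the gain at N = 20.
- At rho 0.7 the half-width falls only from 14.6 to 13.9, and near 0.9 there is nothing to gain.
- For rho up to 0.7, both methods leave half-widths above the 9-point MCIC.
- Efficacy is a secondary aim of a trial sized for feasibility.

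**Conclusion.** The point holds in a limited form: the plan names change as its efficacy contrast, does not pre-specify the baseline score as a covariate, and leaves its use to an optional choice made after seeing the data. If the comparison is run unadjusted, a quite ordinary imbalance of one standard error moves the HOOS-pain estimate by between 0.9 points (rho 0.9) and 6.3 points (rho 0.3), against an MCIC of 9. Relative to ANCOVA, the change analysis carries about 45%, 25% and 11% more variance at rho 0.3, 0.5 and 0.7 (1/0.691, 1/0.797, 1/0.903), and no excess at about 0.9.

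These sizes rest on 10 per arm, SD 20 with equal spread at both visits, and an assumed rho. It would go too far to say that baseline adjustment is excluded, or that it always improves precision at this sample size. The point does not touch the feasibility outcomes or the global change score, which has no baseline value. The change is worth making because the effect estimates are intended for later power calculations and the remedy is almost free.

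**What to change.** For each secondary outcome measured at both visits (HOOS subscales, iHOT-33, hip strength, hip flexion range), pre-specify a linear model of the week-12 score on treatment group and the baseline score of the same outcome. Using change as the response with the same terms is equivalent for the treatment effect. Report the adjusted mean difference with its 95% CI. State that this adjustment is always made and does not depend on the observed influence of any covariate. Reword the efficacy sentence so that it refers to these secondary outcomes and not to the primary ones.

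The cost is analysis wording and one degree of freedom, with a negligible loss of precision if rho is about 0.9 or higher (half-width 8.5 against 8.4). No new data, visits or participants are needed. Trial status reports 16 participants already through follow-up, so the wording should be fixed before any comparison by group is run.

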#### Interventions

Each participant will be treated by experienced physiotherapists who will be trained and proficient in both interventions (physiotherapy and control). The physiotherapists will receive two training sessions prior to the commencement of the study. Monthly meetings between the treating physiotherapists and the project coordinator (JK) will occur throughout the trial to ensure that the physiotherapy intervention remains consistent. The intervention is a face-to-face physiotherapy intervention, which will be delivered in eight sessions over three months (once per week for four weeks, then once per fortnight for eight weeks). This semi-standardised type of intervention has been described previously in an RCT protocol for post-operative physiotherapy in patients with femoro-acetabular impingement [38]. Participants will be asked to refrain from other physiotherapy interventions during the trial. All participants will be able to discuss concerns regarding their condition with the project coordinator (JK) throughout the trial if needed.

